## Abstract

The dose of progressive active mobilization is still uncertain. The purpose of this study is to identify if the addition of a protocol of progressive active mobilization with dose and training load control to usual care is effective in reducing the length of stay in intensive care unit (ICU) and the improvement of the functioning, incidence of ICU-acquired weakness (ICUAW), mechanical ventilation duration and mortality rate in patients hospitalized in ICU. It is Double-blind randomised clinical trial. The setting for this trial will be medical and surgical ICU of a university hospital. The study participants will be 118 patients aged> 18 years admitted to ICU for less than 72 hours. Participants will be randomized to either an experimental or control group. The experimental group will undertake addition of a protocol of progressive active mobilization with dose and training load control to usual care, while the control group will undertake only usual care. The primary outcome will be length of ICU stay. The secondary outcomes will be Cross-sectional area and muscle thickness of the rectus femoris and biceps brachii, Change in muscle strength from the baseline, Functional Status, incidence of ICUAW, Days with mechanical ventilation and Mortality. All statistical analyses will be conducted following intention-to-treat principles. It has a detailed description of the dose of exercise, was designed with the strictest methodological criteria. These characteristics allow to investigate with greater certainty the results progressive active mobilization in critical patients, allowing replication and future combinations in meta-analyzes.

## Introduction

Physical rehabilitation strategies involving active and progressive mobilization protocols have been recommended for the management of critical illness-related morbidity [1]. The strategies focus on reducing the length of stay in an intensive care unit (ICU LOS), preventing prolonged mechanical ventilation [2], increasing mobility and muscle strength, and extending the days alive out of hospital to 180 days [3] in patients hospitalized in an intensive care unit.

Despite the recommendation of early mobilization for critically ill patients, the effects of mobilization are inconclusive. Serious risk of bias, imprecision, and heterogeneity of individual study designs and intervention protocols hamper the ability to achieve a precise and accurate estimate of the effect size and decrease the quality of evidence [4]. Few published randomized clinical trials (RCTs) have adequately described the dose and intensity of the protocols used [4,5]. There is considerable variability in the results of clinical trials evaluating early mobilization [6]. Tipping et al. [3] reported that there is no consistent effect of active mobilization on ICU LOS. According to the authors [3], several studies did not separate the LOS for survivors and non-survivors and the limitations identified in the individual RCTs prevent the pooling of results for meta-analysis.

It is well documented that the exercise dose is a determining factor for the results of exercise programs. Variables such as intensity, execution time and rest, number of repetitions, and progression may influence strength gain and cardiorespiratory capacity [7,8]. Despite the variety of progressive active mobilization protocols, the optimal training scheme has not yet been defined [3,4]. The most important factor influencing outcomes such as LOS, strength, and function may be the addition of a training dose control protocol based on the major international protocols [5] and involving variables of intensity, frequency, number of repetitions, rest time, and progression scheme.

Therefore, the primary endpoint of this RCT will be to identify if the addition of a protocol of progressive active mobilization with dose and training load control to usual care is effective in reducing the length of stay in ICU. The secondary outcomes will be cross-sectional area and muscle thickness of the rectus femoris and biceps brachii, change in muscle strength, functional status, incidence of ICU-acquiredweakness (ICUAW), days with mechanical ventilation, and mortality.

## Methods

The study will use the single-center, randomized controlled trial protocol, with blinding of the assessors and participants, to evaluate progressive active mobilization compared to usual care in the ICU. This is a study of superiority that adhered to the Consolidated Standards of Reporting Trials (CONSORT) recommendations [9] and to Standard Protocol Items for Clinical Trial (SPIRIT) [10]. Clinical Trial Registration Number: NCT03596853.

### Participants

Patients admitted to the ICU of the Universitary Hospital [name] of the Federal University of Bahia (UFBA), Salvador, Bahia, Brazil, who met the eligibility criteria will be recruited in the study. Inclusion criteria: Patients hospitalized in the ICU aged 18 years or more with the following: a minimum functional classification of level 1 (i.e. being able to roll in the bed and bridge); Barthel index [11] recall of at least 70, 2 weeks prior to ICU admission [12]; and the ability to interact with the physiotherapist, determined by at least three positive responses of the following five commands: (1) “Open (close) your eyes,” (2) “Look at me,” (3) “Open your mouth and put out your tongue,” (4) “Nod your head” and (5) “Raise your eyebrows when I have counted to five" [13].

Exclusion criteria included the following: patients with hospitalization time greater than 72 hours before the start of the study; patients with an estimated mortality rate greater than 50% according to Acute Physiology and Chronic Health Disease Classification System II (APACHE II) [12]; patients with increased intracranial pressure or with an history of cardiorespiratory arrest; patients with unstable fractures that hamper the progression of mobilization levels; lower limb amputees; patients with degenerative neuromuscular disease; and those with a history of cerebrovascular accident, traumatic brain injury, or radiotherapy and/or chemotherapy in the last 6 months.

### Randomization and allocation

After the start of the research, all the patients admitted to the ICU will be assessed for inclusion based on the eligibility criteria through daily visits in direct communication with the multidisciplinary team. The patients that met the eligibility criteria will be allocated randomly in the intervention and control groups using the simple randomization strategy [14–16]. The numbers associated with the identities of the eligible patients will be concealed in an opaque, coded, and unidentified envelope [17], which will be signed and dated by the researcher responsible for the allocation. Only the physiotherapist who performed the intervention will know the meaning of the code contained in the envelope and, therefore, will know which patients received the progressive active mobilization protocol. Randomization will be performed by an independent researcher not involved in the study (the independent researcher will not be part of the intervention or the evaluation and will be blinded to the intervention and control codes).

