### Sample size calculations

The sample size calculation will be based on a mean difference in the length of hospital stay of 2.5 days; considering a confidence interval of 95%, power of 80%, and a ratio of 1: 1 between the two groups. Based on the averages of the study by Dong et al. [33] (12.7±4.1 vs 15.2±4.5 days), a sample size of 94 patients was obtained, 47 for each group. After adjusting 20% for missing, death, loss to follow-up, and withdrawals, the corrected sample was 118 subjects. The study by Dong et al. [33] was chosen because it had a population similar to that in the present study. Among other aspects of population similarity, the study involved patients able to perform activities independently and with a probability of <50% for death at 6 months. The sample size calculation will be performed using the module that calculates sample sizes to compare two averages available on the website: https://www.openepi.com/SampleSize/SSMean.htm.

This sample also will be sufficient to contemplate the functional independence objective, based on the percentage of patients returning to their functional state at the time of hospital discharge (FSS = 35). A final sample size of 86 patients was obtained, 43 for each group, based on 50% of patients returning to the previous functional state at the time of hospital discharge [34] and assuming that 80% of the patients remained in the intervention group at the time of hospital discharge.

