### Data analysis

For the analysis of demographic and clinical data, descriptive statistics will be used. The data of continuous variables will be analyzed with measures of central tendency and dispersion. The categorical variable data will be analyzed with frequency measurements. To perform the inferential statistics, tests for normality and homogeneity of variance will be performed. Since the data will be normally distributed, analysis of variance (ANOVA) will be used to compare the mean differences of the variables, followed by the Bonferroni post hoc test. If there will be no normal distribution, the Kruskal-Wallis test will be used, followed by the Mann-Whitney post-hoc test. χ2 tests will be used to evaluate the differences in the categorical variables between the groups.

Kaplan-Meier analysis will be used to estimate ICU LOS, mortality, and mechanical ventilation time, and a log-rank will be used to assess the difference between the groups. Poisson or negative binomial model will be used to estimate the incidence rate ratio. Stratified analyses will be performed according to age, initial functional status, and the Acute Physiology and Chronic Health Enquiry (APACHE-II) score to identify potential confounders. Cohen's *d* effect sizes will be also calculated. Before carrying out the analyzes, test methods assumptions will be verified.

Mean and median differences and 95% confidence intervals will calculated. The significance threshold will be used *P* < .05 for each outcome and testing will be used two-sided. The statistical software used will be used IBM SPSS for Windows 21.0. All study analyses will be used performed according to the intention to treat.

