### Strengths and weaknesses of the study

One of the strengths of the study is the study design, which involved blinding of the patients and functional assessors, presenting an adequate sample for the proposed objectives as well as an adequate description of the interventions offered in both groups. Recently, a Cochrane review [4] described that there is insufficient evidence of good quality to support the benefits of mobilization for improved physical function or performance, muscle strength, and quality of life. The present protocol, based on an individualized prescription and focusing on transference and locomotion, as well as on the monitoring of effort intensity (using the Borg scale), may expose patients to an adequate dose so that the effects of exercise can promote the necessary changes in the cardiorespiratory system and skeletal muscle. Another important point is that the protocol will have an early start and will be based on active mobilization, which will reduce some confounding variables observed when this mobilization is initiated at a later stage.

The protocol has some limitations, such as the fact that it will be performed initially in only one center; furthermore, the ICU had a mixed profile of patients, including clinical and surgical patients. Another confounding variable will be the absence of a prior functional status control for physical exercise.

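### Simple randomisation and the named analysis factors leave the medical/surgical mix, which the protocol itself lists as a limitation, uncontrolled; the cost is precision and credibility, not validity

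*Protocol article*

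**What the plan says.** All references are to the protocol article.

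- **Randomization and allocation:** patients "will be allocated randomly in the intervention and control groups using the simple randomization strategy". No blocks or strata are described. A researcher independent of the intervention and the evaluation performs the randomisation, and opaque envelopes are used.
- **Sample size calculations:** the trial is sized for "power of 80%, and a ratio of 1: 1 between the two groups", on a difference of 2.5 days ("12.7±4.1 vs 15.2±4.5 days), a sample size of 94 patients was obtained, 47 for each group"), raised to 118 for losses.
- **Data analysis:** stratified analyses meant to identify confounders are planned by age, functional status at entry and APACHE-II score. Medical or surgical admission is not among them. For ICU stay, the section allows ANOVA, a rank test, or Kaplan-Meier with a log-rank test.
- **Strengths and weaknesses of the study:** among the limitations, "the ICU had a mixed profile of patients, including clinical and surgical patients. Another confounding variable will be" a further item. The word "Another" is what makes the case mix a confounder in the authors' reading; it is not called one directly.

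**The concern.** The Discussion singles out a patient characteristic as a weakness, but neither the allocation method nor the listed analysis factors deal with it. Whether an ICU admission is medical or surgical is normally known at enrolment, so it could be balanced in advance.

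If the two types of patient stay in the ICU for different lengths of time, two things follow. A chance excess of one type in one arm moves the observed difference for reasons unrelated to mobilisation. And leaving the factor out of the analysis keeps its variation in the error term of a trial planned at only 80% power. At stake are the precision of the primary comparison and its standing with readers, who can raise against it the limitation that the authors state themselves.

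**Working it through.** **Inputs from the protocol article.** Difference 2.5 days; SDs 4.1 and 4.5; two-sided 0.05; power 80%; 1:1; 94 evaluable and 118 randomised. The 2.5 days is worded as hospital stay in Sample size calculations; it is used here, as in the plan, as the target for the primary outcome.

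**Assumptions (not in the documents).** Surgical share 20% to 50%; difference in mean stay between medical and surgical patients 2 to 5 days. The upper value exceeds one SD of stay in the plan.

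**1. The plan's own figure.** Pooled variance = (4.1² + 4.5²)/2 = 18.53, SD 4.305. Per arm n = 2 × 18.53 × (1.960 + 0.842)²/2.5² = 46.5, so 47 per arm and 94 in total. 94/0.8 = 117.5, so 118. The stated size reproduces.

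**2. Arm sizes under simple randomisation.** With the number in one arm Binomial(118, 0.5), the central 95% range is 48 to 70. A difference of 12 or more (53 v 65 or worse) has probability 31%. Power = Φ(2.5/√[18.53(1/n₁ + 1/n₂)] − 1.96), for 94 evaluable patients:

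| Split | Power |
|---|---|
| 47:47 | 80.4% |
| 42:52 | 79.9% |
| 37:57 | 78.6% |

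A split of 37:57 or worse has probability 5.0%. Averaged over all splits, power is 80.0%. Unequal arms therefore hardly matter.

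**3. Gap in surgical share.** Fix the number of surgical patients S among 118. Each patient is allocated by a fair coin, so surgical patients in one arm are Binomial(S, 0.5) and medical patients Binomial(118 − S, 0.5). Summing over all outcomes:

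| Surgical share | S | Gap ≥ 10 points | Gap ≥ 15 points |
|---|---|---|---|
| 20% | 24 | 19% | 4% |
| 30% | 35 | 24% | 8% |
| 50% | 59 | 31% | 12% |

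If S is itself random, simulation gives 18% at a 20% share and 29% at 50% for the 10-point gap, so the answer barely depends on this choice.

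**4. Effect on the ICU-stay difference.** Shift = gap × difference in mean stay.
- 0.10 × 2 = 0.2 day, which is 0.2/2.5 = 8% of the planned effect.
- 0.10 × 5 = 0.5 day, which is 0.5/2.5 = 20%.

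For scale, the standard error of the difference is √(18.53 × 2/59) = 0.79 day with 118 patients and √(18.53 × 2/47) = 0.89 day with 94.

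**5. Avoidable variance.** Share of variance due to admission type = p(1 − p)D²/18.53, taking the plan's variance as the total in the mixed population.
- p = 0.5: 0.25 × 4/18.53 = 5% (D = 2); 0.25 × 25/18.53 = 34% (D = 5).
- p = 0.2: 0.16 × 4/18.53 = 3% (D = 2); 0.16 × 25/18.53 = 22% (D = 5).

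**The case against.** Simple randomisation is a legitimate method. Chance imbalance is random error, already counted in the standard error: the 0.2 to 0.5 day shift is part of the 0.79 to 0.89 day, not an addition to it. A reader might infer that the primary comparison is biased or unprotected. The documents do not support that, because randomisation and the error term keep the type I error at its nominal level. This part of the objection stands.

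A reader might also infer that the plan fails to deliver its 1:1 ratio and loses power. The ratio holds in expectation, and a split as uneven as 42:52 costs half a percentage point. This also stands, and arm size is no reason for the change.

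The Discussion calls the mix a limitation and a confounder only by implication, and it does not predict imbalance between arms. The eligibility criteria narrow the population, and APACHE-II and functional status may capture part of any medical/surgical difference. The 5-day figure has no source in the documents, which is why a range is shown. The analysis plan is not available and may name more factors than the article does.

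What remains is that the allocation method is stated outright, and an analysis plan cannot change how patients were allocated. The stated factor list leaves out the one characteristic that the authors flag.

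**Conclusion.** The point holds as a cheap improvement. The plan names a source of heterogeneity, then neither balances it at allocation nor includes it among its stated analysis factors. A gap of 10 points or more in surgical share is fairly likely, at 19% to 31% over an assumed share of 20% to 50%. Its effect is modest, at 0.2 to 0.5 day for an assumed stay difference of 2 to 5 days. The recoverable variance is small if stays differ by 2 days and considerable if they differ by 5. If medical and surgical patients in this ICU stay equally long, nothing is lost. The conclusion concerns precision and credibility and does not call the validity of the trial into question.

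**What to change.** **Randomization and allocation:** replace simple randomisation with computer-generated permuted blocks of randomly varying, undisclosed size, stratified by medical or surgical admission. The independent researcher would prepare the list, as now. With one centre and two strata, over-stratification is not a concern, and the arms stay close to 59:59.

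**Data analysis:** carry admission type into the primary ICU-stay analysis in a form that fits the test used: as a factor in the ANOVA, or through a stratified log-rank or stratified rank test.

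**If recruitment has begun:** leave the allocation as it is and prespecify the adjustment for admission type before unblinding.

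**Cost:** a new list, two sets of envelopes, somewhat more analysis work, and slightly more predictable allocation, which varying and undisclosed block sizes limit. The sample size stays at 94 evaluable and 118 randomised.

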### Blinding

Patients, ultrasound assessors, and functional outcome evaluators will be blind to allocation of patients in the intervention and control groups.

### Assignment of interventions

The control, the usual care group (UCG), will receive mobilization according to the routine of their service: passive kinesiotherapy (consisting of passive range of motion exercises)for patients with a low level of consciousness who are unable to cooperate and perform voluntary active movements; active exercises and mobility training for cooperative patients capable of performing active movements voluntarily; and eventually, use of electrostimulation and passive orthostatism. There is still no specific institutional protocol for mobilization [18]. The UCG mobilization process will be managed by the hospital's team of physiotherapists and without the influence of researchers. The exercises are individualized, applied at low intensity and according to the patient's tolerance, lasting between 10 and 20 minutes, usually twice a day, 7 days a week.

The patients in the intervention group (IG) will undergo a progressive active mobilization protocol with individual dose control and training load stratified according to functional levels and performance (Fig 1) by appropriately trained physiotherapists. The protocol will be applied by two research physiotherapists who have undergone six months of training and who are not part of the hospital's physiotherapist team. Beyond the progressive active mobilization protocol, the IG will also receive the usual care according to the routine of service. Usual care will be provided as described in the control group.

**Fig 1 pone.0238352.g001:**
[figure not shown]
Progressive active mobilization protocol stratified by functional levels and performance. FSS-ICU = Functional Status Score for the ICU [22]. If need minimal or moderate assistance (FSS-ICU ≥ 3) progresses at functional levels (N_1_, N_2_, N_3_, N_4_); Adequate performance = Able to perform 8 series of each movement, alternating 20 seconds of execution with 10 seconds of rest, without discomfort (Borg < 6; scale 0–10) [20], without increased pain and positive response to the questioning: "*Do you feel good after you do physical activity*?" [21]. If it does not have FSS-ICU ≥ 3, but has adequate performance, maintains functional level and increases training volume. The protocol is applied 5 times a week, once a day added to the usual care. If the patient reports discomfort (Borg > 6), increased pain, will rest for 5 minutes. If there is no normalization of the pain and sensation of exertion perceived in that period of time, the training session will be suspended and performed after 24 hours.

The progressive active mobilization protocol will be applied once a day, five times a week. If the patient performed properly within their functional level but was not able to progress to the next level, then there will be a training volume increase within the level (Fig 1). Performed properly means the patient will be able to complete more than eight series [7] of each exercise and did not present increased sensation of pain [19,20], sensation of perceived exertion within the safety limit of the protocol (Borg ≤ 6; scale 0–10) [19,21] and positive response to the questioning: "Do you feel good after you do physical activity [19,22].

The training will be performed through progressive functional movements: N1 (bridge and rolling for both sides); N2 (transfer from supine to sit on both sides); N3 (transfer from sit to stand); and N4 (walking). According to their functional level, patients will perform, once a day (under direct supervision of the researchers), eight series of each movement, alternating 20 seconds of execution with 10 seconds of rest [7]. Patients will be stimulated to perform the movements with the highest possible speed and by maintaining a maximum Borg of 6 [21].

Patients will be able to progress even if they were not able to perform the movement independently; however, they should have only needed minimal or moderate assistance from one physiotherapist, reflecting a Functional Status Score for the ICU (FSS-ICU) ≥ 3 [23] for a specific activity, like rolling for example. Patients will be able to use a chair with armrests for the sit-and-lift workout and auxiliary devices (crutch, walker and/or cane) for training. If the patient report discomfort (Borg > 6) [21] or increased pain, the patient will be advised to in rest for to 5 minutes. If there is no normalization of pain and perceived effort within 5 minutes, the training session will be suspended and performed again after 24 hours.

After the patient meets the performance criteria to increase the training volume, new exercises will be added following the same criteria of eight series of each movement, alternating 20 seconds of execution with 10 seconds of rest: N_1_ (maximal triple flexion/extension of lower limbs: involving hip, knee and ankle -consists of flexing and extending the lower limbs alternately as far as possible); N_2_ (exercise of trunk rotation and anterior and posterior reach of a ball); N_3_ (sit and stand from a chair throwing a ball on the wall; stepping up and down on a ladder); and N_4_ (crouching/lifting throwing a ball on the wall). In the stepping up and down exercise on the ladder, the patient goes up and down only one step 30 cm high. A ball approximately 70 cm in diameter and 200 g will be used for ball exercises. Before attempting protocol exercises, patients will be instructed on the proper way to accomplish each exercise. Demonstration and realization of up to three slow repetitions of each exercise will be performed. Training will start and stop according to the safety criteria of the expert consensus and the recommendations for active mobilization [24]. The safety criteria are divided into four categories (respiratory, cardiovascular, neurological and others) using a standard color system [24]: red indicates the need for caution, with the risk of an adverse event; yellow indicates that the application of the exercise protocol is possible, but only after further analysis with the ICU multidisciplinary team; and green indicates that the patient is safe to apply the exercise protocol. Changes in conditions and in the direction of trends in respiratory, cardiovascular and neurological variables outside the safety intervals [24] imply the immediate suspension of exercises. If normalization of the altered physiological parameter occurs, within 5 minutes, the exercise protocol is reestablished and monitoring continues. If there is no normalization, the team will be informed and the attempt to apply the protocol will occur after 24 hours.

